### Randomization

Before enrolling the first study participant, a research statistician generated the balanced randomization scheme for treatment allocation at both clinical sites using the R Statistical Package.^21^ This method randomly assigns participants to one of three intervention groups (*N* = 20 per group): 1) tAIH + WALK_tSTIM_, 2) tAIH + WALK_tSHAM_, and 3) Placebo + WALK_tSTIM_ in blocks of 6 participants. Using this scheme, the site coordinator will assign each participant to their respective intervention group in the order in which they complete the walking practice sessions. Although the coordinator informs participants about their possible group assignment, they will be blinded to the treatment they receive (i.e., tAIH or Placebo, WALK_tSTIM_, or WALK_tSHAM_). The clinical raters and trainers will also be unaware of each participant's treatment assignment. Based upon reports from participants blinded during our previous tAIH study,^6^ >75% guessed incorrectly or were uncertain of the breathing intervention received, suggesting that our previous blinding and air delivery methods were effective.

We plan a similar integrity analysis for the stimulation sham protocols (no stimulation). Participants guess the interventions received at the end of each treatment session and indicate their guess confidence using a Likert scale.^22,23^ Using a contingency table and Fisher's exact test, we will determine whether the probability of correct guessing differs from chance.

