### Statistical analysis

We plan to test three subhypotheses using parametric and non-parametric statistical inference methods. Statistical significance corresponds to a *p* value <0.05.

#### Hypothesis 1

Daily tAIH + WALK_tSTIM_ enhances overground walking ability in persons with chronic SCI compared to tAIH + WALK_tSHAM_ or Placebo + WALK_tSTIM_.

We predict a decrease in 10MWT and TUG time and an increase in 6MWT distance relative to baseline after tAIH + WALK_tSTIM_ (vs. Placebo + WALK_tSTIM_, tAIH + WALK_tSHAM_). We quantify walking ability using three outcome measures: change in TUG, 10MWT, and 6MWT relative to baseline assessments. Change in performance on these measures will occur after the last intervention session and again at 1-, 4-, and 12-week post-intervention follow-ups (Fig. 3). We will test three related subhypotheses using a linear mixed model with intervention (tAIH + WALK_tSTIM_, tAIH + WALK_tSHAM_, and Placebo + WALK_tSTIM_) and time (visit number) as the fixed main effects, with subject as random effect, whereas scores for TUG (time), 10MWT (time), and 6MWT (distance) will be considered as repeated measures.^56^

Differences from assessment after completion of the walking practice sessions will be compared between and within interventions at tests (T_1_, T_2_) and follow-ups (1, 4, and 8 weeks post-intervention). If analyses of variance (ANOVAs) reveal significant differences, the Tukey-Kramer *post hoc* test will identify pair-wise differences. If walking performance measures at the end of the walking practice sessions are significantly different between intervention groups, we will use an analysis of covariance. We also plan to fit a linear mixed model to test the magnitude and duration of tAIH priming effects based on linear contrasts after controlling for the study period, baseline primary outcomes, and demographics data.

#### Hypothesis 2

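### Adjustment for the post-practice (T0) walking score is triggered by a significance test, and the article does not say which of its models decides Hypothesis 1

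*Protocol article*

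**What the plan says.** All of the following is in the Protocol article. Under Statistical analysis, Hypothesis 1, three specifications appear for the 10MWT, TUG and 6MWT.

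- **A mixed model** with intervention "and time (visit number) as the fixed main effects, with subject as random effect". No interaction and no baseline score are listed. The comparisons are on change scores: "Differences from assessment after completion of the walking practice sessions will be compared between and within interventions", at T1, T2 and each follow-up.
- **A conditional analysis of covariance:** "If walking performance measures at the end of the walking practice sessions are significantly different between intervention groups, we will use an analysis of covariance".
- **A second mixed model,** introduced as an additional plan, for the size and duration of the tAIH effect, "based on linear contrasts after controlling for the study period, baseline primary outcomes, and demographics data". It has no significance trigger.

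None is named as the analysis that decides Hypothesis 1. Fig. 3 separates a first baseline visit (BL) from T0 at the end of week 2, and the text does not say which one the second model's baseline refers to.

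Under Randomization, a statistician "generated the balanced randomization scheme for treatment allocation at both clinical sites", "in blocks of 6 participants". Participants are assigned in the order in which they finish walking practice. Stratification by site is not stated, and no listed model contains site.

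**The concern.** Because the combined treatments start after walking practice, T0 is the pre-treatment score. Under sound randomisation, any T0 difference between arms is chance. A significance test of that difference examines a null hypothesis already known to be true, and its result then selects the analysis.

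At this sample size the test rarely fires, so adjustment is rarely applied. The precision available from a score scheduled for every participant is then mostly lost. The comparison most exposed is the one with least planned power, against tAIH + WALK_tSHAM.

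The article does not follow the same rule elsewhere: its Hypothesis 2 model includes baseline 10MWT speed without any pre-test.

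Three specifications with no stated order also leave open which estimate is the result. As listed, a model with main effects only gives one group difference averaged over visits, whereas the text promises comparisons at each visit.

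**Working it through.** **Inputs from the Protocol article (Sample size).** SD of 10MWT change 3.0 s in the combination arm and 2.0 s in each comparator; differences of 5.2 s and 3.14 s; 16 completers per group; alpha 0.0167. The alpha is taken as two-sided, since sidedness is not stated. The pre-test is taken at 0.05, the article's general significance level.

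**Assumption.** The correlation r between T0 and the later score is not in the document. It is varied from 0.5 to 0.95, with equal variances before and after.

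**1. Reproduce the planned power.** SE = sqrt(3.0²/16 + 2.0²/16) = sqrt(13/16) = 0.901 s. The noncentral t with Welch degrees of freedom gives 81.5% for 3.14 s and 99.9% for 5.2 s. The article states >81% and >99%, so its figures correspond to an unadjusted change-score test.

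**2. Always adjusting for T0.** Variance of the ANCOVA contrast divided by that of the change-score contrast = (1 + r)/2. Multiplying both SDs by the square root of this ratio, for the 3.14 s contrast:

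| r | (1 + r)/2 | Power | Completers per arm for the original 81.5% = 16 × (1 + r)/2 |
|---|---|---|---|
| 0.5 | 0.75 | 92.0% | 12.0 |
| 0.7 | 0.85 | 88.0% | 13.6 |
| 0.8 | 0.90 | 85.9% | 14.4 |
| 0.9 | 0.95 | 83.7% | 15.2 |
| 0.95 | 0.975 | 82.6% | 15.6 |

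**3. How often the pre-test fires.** Take a one-way F test of three arms of 16, with two arms d SDs apart and the third midway. The noncentrality is 16 × d²/2 and the critical value is F(2, 45) = 3.20. Detection is 10% for d = 0.3, 21% for d = 0.5 and 38% for d = 0.7. Two arms can differ by sqrt(4 × 3.20/16) ≈ 0.9 SD without the test reaching significance.

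**4. The rule as a whole.** Simulation with three arms of 16, 40,000 trials per setting and a pooled-variance test. Arms share a common variance here, so the unadjusted power is about 83.5% rather than the 81.5% of step 1.

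| r | Unadjusted change | Test-then-adjust | Always ANCOVA |
|---|---|---|---|
| 0.5 | 83.7% | 84.3% | 92.5% |
| 0.7 | 83.6% | 84.0% | 88.7% |
| 0.8 | 83.5% | 83.6% | 86.7% |
| 0.9 | 83.4% | 83.3% | 84.5% |

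At r = 0.95 the simulation shows no gain. With no true effect, test-then-adjust rejects in about 1.5% to 1.6% of trials, against a nominal 1.67%.

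**5. What change from T0 leaves behind.** Subtracting T0 removes it with slope 1, where the regression slope is r. A T0 difference D therefore leaves an error of −(1 − r) × D in the change-score contrast. In about 12% to 13% of simulated trials a given pair of arms differed by more than 0.5 SD at T0 with a non-significant pre-test. Where the combination arm was the higher one, the change-score contrast was off by about −0.30, −0.19, −0.12 and −0.07 SD of the T0 score at r = 0.5, 0.7, 0.8 and 0.9. ANCOVA was off by at most about 0.01 SD.

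**The case against.** The strongest reply is that r is probably high. With equal variances, r = 1 − 6.5/(2 × SD0²), where 6.5 is the mean of 3.0² and 2.0² and SD0 is the SD at T0. Then r = 0.5 implies SD0 of about 2.5 s and r = 0.8 about 4 s. That looks narrow for AIS C–D participants who need only be able to walk 10 m without help from another person, in a cohort the article itself calls heterogeneous. Assumed SD0 values of 5, 7.5, 10 and 15 s give r = 0.87, 0.94, 0.97 and 0.99, and power of 84.4%, 82.8%, 82.2% and 81.8% against 81.5%. This stands as a limit on the size of the gain: it may be only 0.3 to 3 points. It does not justify the pre-test.

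Four stronger readings are tempting, and the documents do not support them.

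- **That adjustment happens only after a significant test.** The second mixed model controls for baseline outcomes unconditionally. What is missing is its standing and the meaning of its baseline.
- **That imbalance goes uncorrected.** Change from T0 already subtracts the T0 score. What remains is regression to the mean.
- **That the rule inflates type I error.** Overall it does not. Rates above nominal appear only within the subset of trials selected for a missed imbalance, about 2.4% to 4.3% for the change score at r = 0.9 to 0.5.
- **That the analysis ignores a stratification factor.** Stratification by site is an inference from a scheme produced for both sites. No between-site variance is given, so no effect can be computed.

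It can also be said that an analysis plan commonly fixes the primary model and covariate list, and that the phrase about main effects may be shorthand. That is fair for detail left out. The conditional rule is not left out: it is written down, and an analysis plan following the article would inherit it.

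**Conclusion.** The point holds as a weakness in a stated rule, worth correcting before unblinding. Test-then-adjust has essentially the power of no adjustment at every correlation examined. Against it, always adjusting for T0 gains about 8 points at r = 0.5 (92.5% versus 84.3% simulated), about 3 at r = 0.8, about 1 at r = 0.9 and nothing visible at r = 0.95. These figures rest on an assumed r, equal variances before and after, 16 completers per arm and a two-sided alpha of 0.0167. If repeat walk times correlate at 0.9 or more, the power argument is minor. The remaining reason to change is then that one model, fixed in advance, should decide Hypothesis 1 and supply its by-visit contrasts.

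**What to change.** Delete the sentence that makes the analysis of covariance conditional. For each of the three walking outcomes, name one primary mixed model:

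- values at the visits after T0 (T1, T2 and the follow-ups) as the outcome;
- T0 score (always included), intervention, visit and intervention-by-visit as fixed effects;
- within-participant correlation across visits.

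Take the promised by-visit contrasts from that model. If the additional mixed model is kept, label it as supportive and say whether its baseline is BL or T0 and what study period means.

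Secondary suggestion: add site as a covariate, since the allocation scheme was generated for both sites, and state whether allocation was stratified by site.

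The cost is wording in the analysis plan and a few degrees of freedom. T0 is already a scheduled assessment, so no new data are needed.

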For Aim 2, our sample-size estimate focused on results from a preliminary crossover study (unpublished) that showed that *N* = 3 people with incomplete SCI improved their walking speed after 5 consecutive days of tAIH + WALK_tSTIM_. Two participants achieved an MCID on their 10MWT at post-treatment day 5. However, no participants achieved an MCID after 5 consecutive days of Placebo + WALK_tSTIM,_ where the maximum increase in speed corresponded to 0.03 m/s. We predict that participants will require at least seven sessions of Placebo + WALK_tSTIM_ to achieve an MCID in walking speed. Using bootstrap sampling with replacement, we estimated the standard deviation for the number of sessions to achieve an MCID from our pilot study to be 1.5 days. Assuming that seven Placebo + WALK_tSTIM_ sessions are needed in order to achieve MCID as compared to five tAIH + WALK_tSTIM_ sessions estimated from our pilot data, the statistical power is >95% to detect the group difference to achieve an MCID on the 10MWT, with the sample sizes of 16 per group after 20% dropout.

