Daily tAIH priming enhances the potency of WALK_tSTIM_ on improving walking speed in people with chronic SCI. We quantify potency as the number of tAIH + WALK_tSTIM_ sessions (eight total) needed to achieve the MCID in walking speed.^57^ We assess walking speed with the 10MWT at the end of each training session and predict that those who receive tAIH + WALK_tSTIM_ will achieve an MCID with fewer training sessions than either treatment alone (Placebo + WALK_tSTIM_ or tAIH + WALK_tSHAM_). To test this hypothesis, we will use linear mixed models with number of sessions to achieve the MCID as the outcome with treatment group and 10MWT speed at baseline as fixed effects and participant as the random effect. We anticipate that improvement in walking recovery also will correlate with improved 6MWT, TUG, SCI-FAI, WISCI II, and LEMS scores, suggesting the clinical relevance of this intervention across impairment levels and walking deficits.

#### Hypothesis 3

Daily tAIH+WALK_tSTIM_ does not induce maladaptive changes (spasticity, pain, systemic hypertension, and AD) in persons with chronic SCI. We predict no difference in SCATS, NPRS, CVLT, O-TMT, NBDS, and NBSS scores after daily tAIH + WALK_tSTIM_ compared to baseline. We will use a Friedman two-way repeated-measures ANOVA by ranks to compare these relative scores between and within groups. Changes in these scores relative to baseline are the repeated measures. Intervention (tAIH + WALK_tSTIM_, Placebo + WALK_tSTIM_, and tAIH + WALK_tSHAM_) and time are the fixed main effects, with subject as the random effect. We also predict that tAIH + WALK_tSTIM_ will not elicit a greater incidence of systemic hypertension or AD in persons with chronic SCI.

To test these subhypotheses, we will compare the incidence rates of these maladaptive changes between interventions using the relative risk.^58,59^ A relative risk of 1 will indicate no association between the maladaptive measures and interventions. Using the 95% confidence interval of the relative risk,^59^ we will determine whether there is a statistically significant association between interventions. We predict that the relative risk of hypertension and AD are not different between tAIH versus placebo interventions and WALK_tSTIM_ versus WALK_tSHAM_ interventions.

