### Study limitations

Clinical trials are necessary for the study of combinatorial interventions to treat SCI. However, the experimental protocols for these trials are often beset with study design challenges attributable, in part, to confounding treatment interactions, small sample size, short study duration, and SCI heterogeneity. The study of multiple treatments and their interactions requires the appropriate choice of controls to discriminate between the clinical outcome of the treatments alone, combined, or neither. Identifying the study groups is pivotal to trial success, but requires larger sample sizes. Because of challenges from the ethical perspective in SCI research with humans, we cannot include a control (no treatment) group in the present trial. We anticipate that some participants will receive additional therapy services upon study enrollment.

We will quantify the interactions between frequency/duration of these services and our primary outcome measures. The biostatistician also will use multi-variate statistical models to assess these and other potential confounds to our outcome measures. Though most studies continue for longer periods (e.g., 12 weeks),^61^ up to eight sessions of tAIH or WALK_tSTIM_ are sufficient to elicit improvements in walking speed in persons with SCI.^6,8,62^ To consider the potential long-term effects of tAIH + WALK_tSTIM_ on walking ability, we will follow up at 1, 4, and 8 weeks post-treatment.

Small sample sizes can undermine the translation of results to the larger heterogeneous patient population. We also acknowledge that balancing treatment groups of a heterogeneous SCI cohort will be a challenge. To address this obstacle, we will consider age, sex, reliance on walking aids,^63^ and injury level. Second, we do not yet know the potency of WALK_tSTIM_ and eight sessions may be considered too few to achieve MCID in the treatment groups. We chose eight sessions to remain pragmatic in treatment duration while aligning our study design to a recent placebo-controlled trial that found WALK_tSTIM_ induced clinically significant gains in walking speed within six sessions.^62^ We acknowledge that achieving MCID in eight sessions may not occur during treatments without tAIH. If this happens, we will compare groups using survival-type analyses to include those with no participants who achieved MCID.^64^ Third, medication changes are frequent in persons with SCI, which may alter neural plasticity.

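### Aim 2 names two different tests for sessions-to-MCID, with an unclear, outcome-dependent switch between them and no rule for participants who have not reached MCID by session 8

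*Protocol article*

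**What the plan says.** Under Statistical analysis, Hypothesis 2, the Protocol article defines potency as the number of "sessions (eight total) needed to achieve the MCID in walking speed". For the test, "we will use linear mixed models with number of sessions to achieve the MCID as the outcome with treatment group". The model's other fixed effect is the starting walking speed, and it carries a random effect for each participant. The 10MWT is taken at the end of each training session. The section gives no value and no censoring rule for someone who has not reached MCID after the eighth session.

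The Study limitations section returns to the point: "We acknowledge that achieving MCID in eight sessions may not occur during treatments without tAIH". If that happens, "we will compare groups using survival-type analyses to include those with no participants who achieved MCID".

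The Sample size section supplies the planning figures for Aim 2. On the control arm: "We predict that participants will require at least seven sessions of Placebo" + WALK_tSTIM. The calculation then takes seven sessions against five, and on spread "we estimated the standard deviation for the number of sessions to achieve an MCID from our pilot study to be 1.5 days". With 16 completers per group the stated power is above 95%. The pilot had three participants. Two reached MCID by day 5 on the combination and none did within five days on placebo plus stimulation.

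**The concern.** The number of sessions to MCID is a time to event observed through a window of eight sessions. For a participant still short of MCID after session 8, all that is known is that the count exceeds 8. A linear model needs a number, so the analyst must leave the participant out, assign a score, or change method. The Hypothesis 2 text does not say which, and the Study limitations text changes method under a condition that can be read in two ways.

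The control arm is assumed to need at least seven of eight sessions, so non-achievers should be common there and rare in the combination arm. How they are handled then affects the estimate, the power and possibly the conclusion. A choice made once the achievement pattern is visible also leaves the type I error of the Aim 2 comparison open to question. Aim 2 is one of the two aims on which the sample size rests.

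A lesser point is that each participant contributes one session count. A participant random effect is then confounded with the residual, and the model reduces to ordinary linear regression.

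**Working it through.** **Inputs** (Sample size and Statistical analysis sections): means 5 and 7 sessions, SD 1.5, 16 per arm, significance level 0.05. Assumed here: a two-sided test and a normal latent session number. Only the comparison powered in the protocol (combination vs Placebo + WALK_tSTIM) is checked, without baseline adjustment.

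**1. Reproduce the stated power.** Standard error = 1.5 × √(2/16) = 0.530; standardised difference = 2/0.530 = 3.77. The normal approximation gives Φ(3.77 − 1.96) = 96.5%, and the exact noncentral t with 30 df gives 95.4%. The stated figure of above 95% is reproduced, but as a comparison of two means in which every participant has an observed count.

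**2. Expected share of non-achievers at session 8.** The cut is 8.5 if the latent value is rounded to the nearest session, and 8 if it is rounded up.
- Placebo + WALK_tSTIM: P(N(7, 1.5) > 8.5) = 1 − Φ(1.00) = 15.9%; P(> 8) = 1 − Φ(0.67) = 25.2%. That is about 2.5 to 4 of 16.
- Combination: P(N(5, 1.5) > 8.5) = 1.0%; P(> 8) = 2.3%.

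**3. How often each reading of the fallback would be triggered.**
- At least one non-achiever in the placebo arm: 1 − (1 − 0.159)^16 = 94%; 1 − (1 − 0.252)^16 = 99%.
- No achiever at all in that arm: 0.252^16 is below one in a billion, and it occurred in 0 of 4,000 simulated trials.

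Under the broad reading (any non-achiever) the survival analysis nearly always replaces the linear model. Under the narrow reading (an arm with no achiever) it almost never starts.

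**4. Expected difference if non-achievers are treated as missing.** The mean among achievers is m − 1.5 × φ(z)/Φ(z), with z = (cut − m)/1.5.
- Cut 8.5: 7 − 1.5 × 0.2420/0.8413 = 6.57 and 5 − 1.5 × 0.0262/0.9902 = 4.96; difference 1.6.
- Cut 8: 7 − 1.5 × 0.3194/0.7475 = 6.36 and 5 − 1.5 × 0.0540/0.9772 = 4.92; difference 1.4.

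The planned difference of 2.0 shrinks to 1.4–1.6.

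**5. Power by handling rule** (simulation, 16 per arm, at least 4,000 runs per scenario; t-test for the linear comparison, log-rank censored at session 8):

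| Handling of non-achievers | Plan's inputs (5 vs 7, SD 1.5) | Illustration: 80% vs 30% reach MCID, same timing among achievers |
|---|---|---|
| Treated as missing | 77–87% | about 5% |
| Scored 8 or 9 | about 93–96% | 67–75% |
| Log-rank, censored at 8 | 93–94% | about 82% |

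The 80% and 30% shares are an assumption made for illustration and appear nowhere in the protocol. The illustration shows what happens when the treatment acts mainly by turning non-achievers into achievers.

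**The case against.** The strongest reply is that the protocol has already seen the problem. It anticipates non-achievement and names a survival-type analysis. The conditional phrase can naturally be taken to mean any non-achievement, and the clause about groups with no achiever may describe how far the method reaches rather than what triggers it. On that reading survival analysis would be used in some 94–99% of trials under the plan's inputs. The article is also a condensed document, and scoring and censoring details may sit in a full plan that is not shown.

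A reader might infer something stronger: that non-achievers drop out of the linear model, so that only achievers are compared and a real effect could vanish. The documents do not support this as a statement of what is planned. The only exclusion rule, in the Statistical analysis section, concerns participants who miss more than two sessions. Missing is the software default for an undefined outcome, but scoring non-achievers 8 or 9 is equally compatible with the text and costs almost no power on the plan's inputs. Nor is the near-total loss of power in the illustration a consequence of the protocol's figures, which assume a difference in timing.

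The random-effect point is also minor: it is redundant specification and does not bias the group comparison.

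What survives is that the article does not leave the method open. It names two methods in two places, makes the choice depend on observed outcomes, and words the trigger ambiguously. The fallback also speaks only of treatments without tAIH, which describes one of the three arms; non-achievers in the two tAIH arms are not mentioned.

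**Conclusion.** The point holds as a defect of specification. The test named for Aim 2 does not suit an outcome censored at session 8, and the survival alternative is conditional, ambiguous and dependent on the results. It is not established that participants will be excluded.

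On the plan's inputs the consequence ranges from negligible (scored 8 or 9) to a fall in power from about 95% to 77–87% (treated as missing). If the arms differ mainly in who reaches MCID rather than when, the handling rule could decide the conclusion.

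These sizes rest on normality, a two-sided 0.05 level and an SD bootstrapped from three people. The seven-session control figure is stated as a minimum, so the non-achieving share could be higher than 16–25%. Aim 1 is unaffected. This should be fixed before the data are unblinded, but it does not undermine the trial's design.

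**What to change.** Name one time-to-event analysis as the single Aim 2 test for all three arms: a log-rank test, or discrete-time or Cox regression adjusted for the starting 10MWT speed that is already planned as a covariate. Censor at session 8 or at the last attended session. Report the proportion reaching MCID in each arm beside the session counts. Remove the linear mixed model from Hypothesis 2 and the conditional switch from Study limitations, so that both sections describe the same analysis.

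The cost is wording only. The 10MWT is already measured at each training session, so no visit, measurement or change in sample size is needed. On the plan's inputs the log-rank test keeps about 93–94% power, slightly under the stated figure of above 95%, and the power statement should be updated to match.

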**FIG. 3. f3:**
[figure not shown]
Timeline of interventions and assessments. After the initial screening visit (S), each intervention consists of eight sessions of walking training (WALK) alone, followed by eight additional sessions of tAIH or Placebo before WALK_tSTIM_ or WALK_tSHAM_. Assessments occur at baseline (BL), at the end of intervention weeks 2 (T_0_), 3 (T_1_), and 4 (T_2_), and, again, after 1 (F_1_), 4 (F_4_), and 8 weeks (F_8_) after the last intervention session. tAIH, therapeutic intermittent hypoxia; WALK_tSTIM_, transcutaneous spinal stimulation-enhanced walking therapy.

We anticipate that tAIH before WALK_tSTIM_ will exceed the benefits of walking practice (WALK), tAIH + WALK_tSHAM_, or Placebo + WALK_tSTIM_ on enhancing the performance of the trained task of overground walking. Justification for the treatment sequence of tAIH followed by WALK_tSTIM_ is based on the estimated time (minutes) required for tAIH to facilitate expression of BDNF.^27^ Applying tAIH ∼1 h before WALK_tSTIM_ may promote temporal alignment of mechanisms of WALK_tSTIM_ neuromodulation with complementary mechanisms of tAIH-induced plasticity that involve BDNF. Details on these interventions are below.

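### Hypothesis 3 words its prediction for six safety scores as no change from baseline within the combination arm, which cannot separate harm from continued walking practice and retesting; the expectation of exceeding WALK likewise has no concurrent comparator

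*Protocol article*

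**What the plan says.** All references are to the protocol article.

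- **Statistical analysis, Hypothesis 3.** The prediction for spasticity, pain, cognition, bowel and bladder is: "We predict no difference in SCATS, NPRS, CVLT, O-TMT, NBDS, and NBSS scores after daily tAIH + WALK_tSTIM_ compared to baseline". The analysis that follows is a Friedman test "to compare these relative scores between and within groups", with intervention and time named as factors. For hypertension and autonomic dysreflexia (AD), "we will compare the incidence rates of these maladaptive changes between interventions using the relative risk", with a 95% confidence interval.
- **Statistical analysis, Hypothesis 1.** The hypothesis is stated against the two comparator arms. The section adds: "Differences from assessment after completion of the walking practice sessions will be compared between and within interventions at tests" T1 and T2 and at the follow-ups.
- **Experiment protocol, text under Fig. 3.** The authors anticipate that the combination "will exceed the benefits of walking practice (WALK"), listed beside the two comparator arms.
- **Experiment protocol and intervention sections.** Eight WALK sessions come first. Eight treatment sessions follow, in which every arm walks for 45 minutes with active or sham stimulation. The arms are tAIH + WALK_tSTIM, tAIH + WALK_tSHAM and Placebo + WALK_tSTIM.
- **Table 2 and Cognitive ability.** SCATS, NPRS, NBDS and NBSS are taken at baseline, at testing sessions and at follow-up. CVLT3 and O-TMT are taken only at T0 and T2.
- **Study limitations.** On ethical grounds, "we cannot include a control (no treatment) group in the present trial".

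**The concern.** The randomised question on safety is whether tAIH or tSTIM does harm beyond what walking, retesting and time do. A before-after change within one arm does not ask that. If walking eases spasticity or pain, or a second cognitive test goes better because it is the second, the gain offsets a harm and the sum can read as no difference. Safety is a named aim (Aim 3), so the wording of its prediction decides what may be concluded.

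The benefit side has the same structure. WALK alone exists only as the eight sessions before treatment. A gain after T0 within an arm contains eight further walking sessions, so it cannot be credited to treatment over and above WALK.

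**Working it through.** **1. What each change contains.** Write S for the shared change (practice, retest, time). Relative to walking with placebo and sham, write c for the effect of the combination, a for tAIH alone and s for tSTIM alone.

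- Within the combination arm: change = S + c.
- Combination minus Placebo + WALK_tSTIM: (S + c) − (S + s) = c − s, the added effect of tAIH.
- Combination minus tAIH + WALK_tSHAM: (S + c) − (S + a) = c − a, the added effect of tSTIM.

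S drops out only from the arm contrasts. For SCATS, NPRS, NBDS and NBSS, S from baseline to T2 covers eight WALK-only sessions, eight treatment-phase walking sessions and the repeat assessments. For CVLT3 and O-TMT there is no earlier value than T0, so S covers the treatment-phase walking and one retest; the WALK-only sessions are outside it.

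**2. The plan's own power.** Inputs from Sample size: 16 completers per arm, SD 3.0 s (combination) and 2.0 s (comparators), alpha 0.0167, differences 5.2 s and 3.14 s. Two-sided testing is assumed.

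- Standard error = √((9 + 4)/16) = 0.901 s.
- Noncentrality: 5.2/0.901 = 5.77 and 3.14/0.901 = 3.48; critical t (30 df) = 2.535.
- Power = 99.9% and 82.2% (81.5% with Welch degrees of freedom).

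The stated figures of above 99% and above 81% reproduce. They concern arm contrasts only; no power is stated for the safety scores or for a comparison with WALK alone.

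**3. Within-arm gain with no treatment effect.** The practice gain g is an assumption; the article gives none for the second eight sessions. One-sample t-test, n = 16, two-sided 0.05, critical t (15 df) = 2.131, noncentrality = g × √16/SD.

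| Assumed 10MWT gain | SD 3.0 s (combination arm) | SD 2.0 s (comparator arms) |
|---|---|---|
| 0.5 s | noncentrality 0.67: 10% | 1.00: 16% |
| 1.0 s | 1.33: 24% | 2.00: 47% |
| 2.0 s | 2.67: 70% | 4.00: 96% |

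Each percentage is the chance of a significant within-arm result when neither tAIH nor tSTIM does anything. A between-arm test stays at 5%. The SD 3.0 s column is the relevant one for the combination arm.

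**4. Harm on the safety scores.** The article gives no SD or retest effect for them, so these figures are assumptions in units of the SD of change, two-sided 0.05.

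- Within arm, n = 16: 95% confidence half-width = 2.131/√16 = 0.53 SD.
- True worsening of 0.5 SD, no shared gain: power 0.465, so missed about 53% of the time.
- Same worsening with a shared gain of 0.25 SD: net 0.25 SD, power 0.155.
- Same worsening with a shared gain of 0.5 SD: net zero, so only the 0.05 error rate remains. This follows by construction and marks the extreme.
- Between arms, 16 against 16: half-width = 2.042 × √(2/16) = 0.72 SD; power for 0.5 SD is 0.28, whatever the shared gain.

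**The case against.** **Between-arm safety comparisons are already planned.** This stands. The scores are to be compared between as well as within groups, and hypertension and AD by relative risk between arms. A reader might infer that within-arm change is the only safety evidence; the Hypothesis 3 text does not support that.

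**The plan never says that within-arm change will prove benefit beyond WALK.** This also stands. Hypothesis 1 names only the two comparator arms, tests them in a model with intervention as a factor, and only those contrasts are powered. The sentence under Fig. 3 is an anticipation, not a decision rule. A reader might join it to the within-intervention comparisons and conclude that Hypothesis 1 rests on before-after change; it does not. What remains is an expectation that the design cannot test and that Study limitations, while conceding the lack of an untreated control, does not withdraw.

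**Arm contrasts can hide harm, because each comparator shares one component.** This is partly right. Both c − s and c − a vanish only if c = a = s, that is, if either component alone produces the full harm. Otherwise a tAIH harm shows against Placebo + WALK_tSTIM, or a tSTIM harm against tAIH + WALK_tSHAM. That is a reason to keep reporting within-arm change, not to test safety with it.

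**The illustration is soft.** Fair. The one documented figure for placebo plus walking is 0.9 s slower than baseline, which points away from a practice gain, and no offsetting gain in pain, bowel or bladder scores is documented. The planned walking analysis is a mixed model with Tukey-Kramer comparisons, not a separate one-sample test. The percentages show sensitivity to an assumption; they are not forecasts.

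**Conclusion.** The point holds for the stated prediction on SCATS, NPRS, CVLT, O-TMT, NBDS and NBSS: no change from baseline within the combination arm does not show absence of harm. It does not extend to the hypertension and AD comparisons or to the main Hypothesis 1 contrasts. The confounding itself follows from the design and needs no assumption; only its size does. Under the assumptions shown, a 0.5 SD worsening is missed about 53% of the time with no shared gain and more often with one. A walking gain of 0.5 to 2.0 s would make the combination arm's within-arm 10MWT change significant in 10% to 70% of trials with no treatment effect. Separately, the expectation of exceeding WALK has no concurrent comparator, and changes from T0 within an arm cannot support it.

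**What to change.** - Reword the Hypothesis 3 prediction so that the six scores are judged by between-arm differences in change from T0: combination against Placebo + WALK_tSTIM for tAIH, and against tAIH + WALK_tSHAM for tSTIM, each with an estimate and confidence interval. Every one of these scores is scheduled at T0.
- Obtain those contrasts from a method that compares arms, such as a model with arm and arm-by-time. The Friedman test ranks within each participant, so it does not supply them: adding a constant of 100 to half of a simulated sample left its statistic at 3.15 (p = 0.533).
- Keep within-arm change as a descriptive report of the total change under the combination, not as a test of safety or of benefit beyond WALK.
- Drop the expectation of exceeding WALK under Fig. 3, or mark it as not testable in this design.

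Cost: no new data or participants. The price is precision: power about 0.28 against 0.465 within arm for a 0.5 SD worsening with no shared gain. The contrasts also show only the added effect of each component, not the total effect of the combination.
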